## Abstract

**Background:**

Ulcerative colitis (UC) is a chronic non-specific inflammatory intestinal disease, categoried under "dysentery" and "intestinal bleeding" in Traditional Chinese Medicine (TCM). Jianpi Qingchang decoction (JPQC) is a combination formula specifically designed for the treatment of UC. The primary objective of this study is to examine the clinical efficacy of JPQC in individuals diagnosed with UC who exhibit both spleen deficiency and dampness-heat syndrome, along with the presence of fatigue. The investigation will focus on assessing the impact of JPQC on the gut microbiota and metabolites in these patients, aiming to elucidate the regulatory mechanism that JPQC exerts on the gut microbiota and metabolites in the context of UC-related fatigue.

**Methods:**

In this randomized clinical trial, 140 subjects diagnosed with UC will be recruited and randomized into two groups. They will receive either JPQC combined with mesalazine or mesalazine alone for 12 weeks. Follow-up visits will be conducted every four weeks, with a post-treatment visit scheduled at 6 months. The primary outcome measures include the Inflammatory bowel disease fatigue scale(IBD-F). Secondary efficacy indicators comprise the assessment of TCM syndrome and individual syndrome efficacy before and after treatment, Modified Mayo score, Simple clinical colitis activity index (SCCAI), as well as the Inflammatory Bowel Disease Questionnaire (IBDQ) for each group. The other outcomes are the Intestinal microbial diversity and non-targeted metabonomics, which will be measured at baseline and 12 weeks after randomization.

**Discussion:**

If effective, JPQC will provide substantial clinical evidence concerning the effectiveness and safety in the treatment of patients with UC experiencing spleen deficiency and dampness-heat syndrome accompanied by fatigue.

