**Fig. 1 fig1:**
[figure not shown]
The flow chart of the trial.

This is a randomized controlled multicenter clinical trial comprising two parallel groups. From January 2024 to June 2025, 140 patients meeting the diagnostic criteria and syndrome types of UC will be recruited. During the recruitment process, potential participants meeting the inclusion criteria will be thoroughly informed about the study's purpose, examinations, intervention measures, and follow-up procedures. Upon obtaining informed consent, eligible subjects will be randomly assigned to two groups in a 1:1 ratio. The groups will receive either JPQC combined with mesalazine or mesalazine intervention for 12 weeks. The UC patients will be followed up again after 6 months. The schedule details are listed in Table 1.

**Table 1 tbl1:** Schedule of trial.

Period	enrollment	baseline	treatment			follow-up
time points	week-1	week 0	week 4	week 8	week 12	week 24
patients						
Informed consent	✓					
Inclusion/Exclusion criteria	✓					
Medical history	✓					
Physical examination	✓					✓
Laboratory examination	✓					✓
Randomization	✓					
Intervention						
Jianpi Qingchang decoction(JPQC) group	JPQC:two times daily; + mesalazine: 1g/three times daily					
Mesalazine control group	1g/three times daily					
Outcomes						
Inflammatory bowel disease fatigue scale(IBD-F)		✓	✓	✓	✓	✓
Inflammatory Bowel Disease Questionnaire (IBDQ)		✓	✓	✓	✓	✓
TCM symptom efficacy		✓	✓	✓	✓	✓
Modified Mayo score		✓			✓	✓
Simple clinical colitis activity index (SCCAI)		✓				
Intestinal microbial diversity and non-targeted metabonomics		✓			✓	
Trial evaluation						
Safety of medicine		✓	✓	✓	✓	✓
Adverse event		✓	✓	✓	✓	✓
Reasons of drop-outs or withdrawals		✓	✓	✓	✓	
Patient's compliance					✓	

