#### The experimental group

2.3.1

The experimental group receiving JPQC combined with mesalazine. JPQC decoction pieces, sourced from the hospital's herbal medicine room, will be administered twice a day, 0.5 h after breakfast and dinner. Mesalazine enteric-coated tablets, 1.0 g per dose, will be given three times a day, 1 h after each meal. The interval between taking JPQC and Mesalazine tablets is 0.5 h.

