#### The control group

2.3.2

The control group receiving mesalazine alone.

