#### Primary outcome

2.4.1

The primary outcome of the study is the inflammatory bowel disease fatigue scale(IBD-F), which will be measured at baseline and 4, 8, 12 weeks after randomization. The IBD-F consists of 3 parts. Possible scores are 0–20 and 0–120 in part I and II, respectively. If the ‘not applicable – N/A’ (not applicable) option is checked (questions 3, 4, 9, 12, 13, 14), a corrected result has to be calculated from the following formula: Corrected result = actual total result/(120 – number of N/As × 4) × 120 [19].

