## Discussion

3

Fatigue, as a concurrent symptom of UC, is frequently overlooked due to its intricate and subjective nature, posing challenges for medical staff. Nevertheless, fatigue not only exacerbates UC symptoms but also significantly impacts patients' quality of life. Clinicians should prioritize attention to the fatigue symptoms experienced by patients with UC to ensure comprehensive and effective care [23].

The etiology of fatigue in UC remains unclear. Drawing insights from research on fatigue mechanisms in other diseases, it is proposed that fatigue may result from various factors, primarily associated with the activation of the immune system, disease activity, and the release of pro-inflammatory factors [8,24,25]. Dysbiosis of gut microflora, a known contributor to gut inflammation, is now implicated in regulating fatigue through the gut–brain axis, which involves two-way communication between the gastrointestinal tract and central nervous system and gut microbes and the immune system [26]. Tryptophan metabolites [27] and polyphenol metabolites [28] have shown promise in alleviating fatigue. A prospective study suggested that microbiome- and metabolite-directed therapies reduce fatigue and depression in patients with IBD [29].

The multifaceted nature of fatigue in UC suggests the existence of different subtypes, requiring tailored intervention measures.

Despite advancements in clinical research, addressing nutrient deficiencies and using immunomodulators or biological agents to reduce systemic inflammation may not entirely alleviate UC fatigue. Studies indicate that biopharmaceuticals and small molecular drugs used for IBD, including ustekinumab, infliximab, natalizumab, tofacitinib, and upatinib, have limited efficacy in relieving fatigue [30]. Even selective JAK1 inhibitors like upatinib, while showing a significant effect on UC fatigue through long-term maintenance, lack clarity on the extent of their impact [31]. Despite the potential connection between nutrient deficiency and fatigue, there is no evidence supporting fatigue improvement in the long-term maintenance of 300 mg thiamine therapy [32], excessive use of vitamin B12 [33], and maltol iron [34] supplementation in IBD fatigue.

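### An unmasked add-on comparison on patient-rated fatigue estimates the effect of adding JPQC openly, not the efficacy of JPQC itself, yet the objective and conclusion claim the latter

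*Protocol article*

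**What the plan says.** **Objective and conclusion.** The abstract's Background states: "The primary objective of this study is to examine the clinical efficacy of JPQC". The abstract's Discussion says that, if the treatment is effective, "JPQC will provide substantial clinical evidence concerning the effectiveness and safety" in the target population.

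**Arms.** Section 2.3.1: "The experimental group receiving JPQC combined with mesalazine", with the decoction taken twice a day. Section 2.3.2: "The control group receiving mesalazine alone". The abstract's Methods gives the same contrast, and Table 1 lists only the mesalazine regimen for the control arm. No placebo or dummy decoction appears anywhere.

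**Design label.** Section 2.1: "This is a randomized controlled multicenter clinical trial comprising two parallel groups". The article uses no term for blinding and never calls the trial open-label.

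**Primary outcome.** Section 2.4.1: "The primary outcome of the study is the inflammatory bowel disease fatigue scale(IBD-F"), measured at baseline and weeks 4, 8 and 12. It is a questionnaire with a not-applicable "option is checked (questions 3, 4, 9, 12, 13, 14"). Section 3 says that fatigue "is frequently overlooked due to its intricate and subjective nature".

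**Other outcomes.** These are IBDQ, the TCM symptom score, the modified Mayo score and SCCAI (section 2.4.2), and stool microbiota and metabolites (section 2.5). Section 3 names no limitation arising from the lack of a placebo.

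**The concern.** The patients who rate the primary endpoint know whether they are taking the decoction. If that knowledge changes how they feel or report fatigue, the between-arm difference contains it, and nothing in the design separates it from an effect of the herbs. The stated objective and conclusion attribute the whole difference to JPQC.

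At stake is what the trial may conclude. A significant IBD-F result could be reported as evidence of efficacy when part or all of it reflects expectation or reporting. IBDQ and the TCM symptom score rest largely on the same patients' reports, so their agreement with IBD-F could be mistaken for independent confirmation.

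**Working it through.** **Step 1. Can patients be masked?** Sections 2.3.1 and 2.3.2, the abstract's Methods and Table 1 agree: one arm drinks a decoction twice a day, the other receives mesalazine only. The control regimen is stated outright, so this is not a detail left to a fuller document. A full protocol could add blinded assessors or a blinded statistician. It could not mask patients without a placebo decoction, and that would contradict these sections.

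**Step 2. Is the primary outcome exposed?** The article does not use the word self-reported. Two statements point that way: IBD-F has response options to check (section 2.4.1), and section 3 describes fatigue as subjective. I take IBD-F to be the patient's own rating.

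**Step 3. What does the contrast estimate?** Both arms receive mesalazine, so the expected IBD-F difference is (effect of JPQC) + (effect of knowing one takes it). The trial estimates the sum and cannot identify the first term alone.

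**Step 4. The plan's sample size.** Section 2.2.6 gives n = 2·p̄·q̄·(Zα+Zβ)²/(p1−p2)², with rates 0.71 and 0.9412 and β = 0.10.
- p̄ = (0.71 + 0.9412)/2 = 0.8256, q̄ = 0.1744, 2p̄q̄ = 0.2880, (p1−p2)² = 0.2312² = 0.05345.
- Two-sided 0.05: 0.2880 × (1.960 + 1.282)² / 0.05345 = 56.6, matching the stated 56 or so.
- One-sided 0.05, as the text says: 46.1, which does not match. That is a separate matter, and this point does not depend on it.
- Dropout: 56/0.80 = 70 per arm, 140 in total, as stated.

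**Step 5. Illustration of size.** The article gives no IBD-F SD and no expectation effect, so the shifts below are assumptions. Let the true JPQC effect be zero, and let lack of masking shift IBD-F by d SD in favour of JPQC. For a two-sample t-test with n per arm, the noncentrality is d·√(n/2) on 2n−2 degrees of freedom. With n = 56 and d = 0.2 it is 0.2 × √28 = 1.06, against a critical value of 1.98. Chance of a significant result favouring JPQC, two-sided α = 0.05:

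| Assumed shift (SD) | 56 per arm | 70 per arm |
|---|---|---|
| 0 | 2.5% | 2.5% |
| 0.2 | 18% | 22% |
| 0.3 | 35% | 42% |
| 0.5 | 75% | 84% |

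At one-sided 0.05, the normal approximation with 56 per arm gives 28%, 48% and 84%, against a nominal 5%.

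**Step 6. Could other outcomes separate the two terms?**
- IBDQ (section 2.4.2.1) and the TCM symptom score (section 2.4.2.2, which includes pain, tenesmus, appetite and fatigue) share the exposure.
- SCCAI is ticked at baseline only in Table 1, so as scheduled it cannot show a treatment effect.
- The modified Mayo score is scheduled at baseline, week 12 and week 24. The article does not list its items. An endoscopic component would depend less on patient report, as would the stool measures, but neither measures fatigue.

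**The case against.** The strongest reply is that a randomised add-on comparison against the same background drug is a legitimate question, and a positive result does support a statement about it. The abstract's Methods states the contrast openly, and its Discussion is conditional on the treatment being effective. This stands. A reader might infer that a positive IBD-F result would support nothing. The documents do not bear that out: it would support the narrower statement that adding JPQC openly to mesalazine led to better reported fatigue than mesalazine alone. Giving JPQC only with mesalazine is not a defect either, since both arms receive mesalazine.

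A reader might also infer that every outcome is biased. That goes too far: the stool measures and any endoscopic Mayo component depend less on report, and section 3 gives the effect on flora and metabolites as the primary aim. These outcomes still cannot establish an effect on fatigue.

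Extra clinical attention in the JPQC arm is another tempting inference. Table 1 gives one visit schedule for both arms, so the documents do not support it.

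Finally, the illustrative shifts are assumed, and bias of that size would matter in any trial this large. That is correct. The table shows what is at risk; it does not predict what will happen. The argument in steps 1 to 3 does not need it.

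None of this answers the mismatch between the claim and the contrast.

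**Conclusion.** The point holds in a limited form. As described, patients are unmasked and the primary outcome is their rating of a subjective symptom. A positive difference would therefore estimate the effect of adding unmasked JPQC to mesalazine, including any expectation or reporting effect, and could not be credited to JPQC's own pharmacological efficacy. The objective and conclusion in the abstract go further than that.

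The size of any bias is unknown. If the decoction were inert and the shift were 0.2 to 0.5 SD, about 18% to 75% of trials with 56 patients per arm would favour JPQC significantly at two-sided 5%, against a nominal 2.5%. This rests on the assumed shifts, equal SDs and complete data on 56 per arm. The conclusion about attribution rests only on the arms and outcome as the article describes them.

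**What to change.** Keep the arms, sample size and visits, and change the wording.

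1. In the abstract's Background, restate the objective as the effect on patient-reported fatigue of adding unmasked JPQC to mesalazine, compared with mesalazine alone, including any expectation effect.
2. Restate the conclusion in the abstract's Discussion in the same terms, and drop the attribution to JPQC's own effectiveness.
3. State that improvement in IBDQ (a higher score) or in the TCM symptom score (a lower score) shares the same potential bias and will not be read as independent confirmation.
4. State that the endoscopic Mayo component and the stool measures depend less on patient report but do not measure fatigue.

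Having questionnaires completed before the patient sees the physician might limit interviewer influence. It would not remove the patient's own knowledge of allocation, so it cannot replace the restated claim.

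The cost is a few sentences and a less favourable claim. No placebo, staff or patients are added.

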**Trial registration:**

ChiCTR2300068348.

## Introduction

1

Ulcerative colitis (UC) is a chronic, non-specific inflammatory intestinal disease primarily affecting the colorectal mucosa and submucosa, categorized under inflammatory bowel disease (IBD). It is estimated that the global prevalence of ulcerative colitis will reach 5 million cases in 2023, with a rising incidence worldwide [1]. The main clinical symptoms of UC include persistent or frequent episodes of diarrhea and mucous purulent and bloody stools. These symptoms may be accompanied by systemic manifestations such as abdominal pain, acute diarrhea, and fatigue.

Fatigue, characterized by a disproportionate lack of energy or exhaustion to physical exertion, adversely affects daily activities and cannot be alleviated by rest [2]. It is a multifaceted, multifactorial symptom associated with various chronic diseases [3]. Notably, Fatigue is a significant clinical symptom for patients with IBD [4], reaching a prevalence of 86 % in those with active IBD and 50 %–52 % in those with mild to inactive IBD [5]. In Chinese patients with UC, the prevalence rate of fatigue is 61.8 %, with higher rates in active disease (68.2 %) than in remission (40.0 %). Factors such as Montreal classification, disease activity, and anxiety are linked to an increased risk of fatigue risk Background [6]. The presence of fatigue in patients with UC is associated with a diminished quality of life [7]. Addressing fatigue is crucial not only for improving the care and quality of life for patients with UC but also for reducing direct medical expenses and the indirect economic impact on work productivity and function [8]. Therefore, it is particularly important to find practical and effective ways to intervene fatigue for improving the care and quality of life of patients with UC.

Traditional Chinese medicine (TCM) posits that the weakness of the spleen and stomach, exogenous pathogens, improper diet, and emotional disorders can contribute to UC. The disease primarily affects the large intestine and is characterized by spleen deficiency, and dampness-heat, blood stasis, and phlegm-dampness. UC is further categorized into seven syndrome types, such as spleen deficiency and dampness accumulation syndrome, large intestine damp-heat syndrome, excessive heat toxin syndrome and liver depression and spleen deficiency syndrome, with spleen deficiency and dampness accumulation syndrome and large intestine damp-heat syndrome being common [9]. In our previous study, we observed varying degrees of fatigue symptoms in patients with damp-heat syndrome of the large intestine and spleen deficiency and dampness accumulation syndrome. Fatigue was notably more prevalent and severe in the latter. Patients with UC and damp-heat syndrome of the large intestine exhibited symptoms such as "stagnation of wetness-evil," characterized by a heavy head, heavy body sleepiness, and sore limbs, among which heavy body sleepiness is its representative symptom. In contrast, patients with UC with spleen deficiency and dampness accumulation syndrome manifested "weakness" symptoms, including listlessness, fatigue, and weakness of limbs, among which fatigue and weakness are its characteristic symptoms. This finding holds significant guidance for clinical syndrome differentiation and the treatment of UC-related fatigue. The methods involving clearing heat and eliminating dampness, invigorating the spleen, and benefiting qi, as explored in this study, offer valuable insights into therapeutic approaches for managing UC-related fatigue [10]. Guided by the principles of invigorating the spleen and qi, clearing away heat and toxic materials, cooling blood and stopping bleeding, and regulating qi and relieving pain, we formulated and optimized Jianpi Qingchang decoction (JPQC) consisting of *Astragalus membranaceus (Huang Qi)30**g, Portulaca oleracea (Ma Chi Xian)30g, Codonopsis pilosula (Dang Shen)15g, Coptidis Rhizoma (Huang Lian)3 g, Sanguisorba officinalis (Sheng Di Yu)15g, Panax notoginseng (San Qi)6g, Bletilla striata (Bai Ji)3g, Radix Aucklandiae (Mu Xiang)6g, and Radix Glycyrrhizae (Sheng Gan Cao)6g* [11]. Forty-four phytochemicals, including astragaloside A, oleracein A, and coptisine, were identified from JPQC using the ultra-high performance liquid chromatography-quadrupole time-of-flight mass spectrometry (UPLC-Q-TOF/MS) method [12]. Our previous study revealed that JPQC effectively alleviated clinical symptoms of abdominal pain and diarrhea in patients with mild-moderate UC, improved mental fatigue, and increased quality of life [13,14]. However, there is a limited exploration of the impact of JPQC on fatigue in patients with UC with spleen deficiency and dampness-heat syndrome. Consequently, we have designed a randomized controlled clinical trial to comprehensively investigate the effectiveness and safety of JPQC in treating patients with UC with spleen deficiency and dampness-heat syndrome accompanied by fatigue. This research aims to contribute valuable insights into potential therapeutic interventions for addressing fatigue in patients with UC, particularly those with spleen deficiency and dampness-heat syndrome.

## Materials and methods

2

### Study design

2.1

The research protocol obtained approval by the Ethics Committee of Shanghai Hospital of Integrated Traditional Chinese and Western Medicine affiliated with Shanghai University of Traditional Chinese Medicine (2022-053-1) and was registered in the Chinese Clinical Trial Registry on February 15th, 2023 (ChiCTR2300068348). The flow chart of the trial is depicted in Fig. 1.

**Fig. 1 fig1:**
[figure not shown]
The flow chart of the trial.

This is a randomized controlled multicenter clinical trial comprising two parallel groups. From January 2024 to June 2025, 140 patients meeting the diagnostic criteria and syndrome types of UC will be recruited. During the recruitment process, potential participants meeting the inclusion criteria will be thoroughly informed about the study's purpose, examinations, intervention measures, and follow-up procedures. Upon obtaining informed consent, eligible subjects will be randomly assigned to two groups in a 1:1 ratio. The groups will receive either JPQC combined with mesalazine or mesalazine intervention for 12 weeks. The UC patients will be followed up again after 6 months. The schedule details are listed in Table 1.

**Table 1 tbl1:** Schedule of trial.

Period	enrollment	baseline	treatment			follow-up
time points	week-1	week 0	week 4	week 8	week 12	week 24
patients						
Informed consent	✓					
Inclusion/Exclusion criteria	✓					
Medical history	✓					
Physical examination	✓					✓
Laboratory examination	✓					✓
Randomization	✓					
Intervention						
Jianpi Qingchang decoction(JPQC) group	JPQC:two times daily; + mesalazine: 1g/three times daily					
Mesalazine control group	1g/three times daily					
Outcomes						
Inflammatory bowel disease fatigue scale(IBD-F)		✓	✓	✓	✓	✓
Inflammatory Bowel Disease Questionnaire (IBDQ)		✓	✓	✓	✓	✓
TCM symptom efficacy		✓	✓	✓	✓	✓
Modified Mayo score		✓			✓	✓
Simple clinical colitis activity index (SCCAI)		✓				
Intestinal microbial diversity and non-targeted metabonomics		✓			✓	
Trial evaluation						
Safety of medicine		✓	✓	✓	✓	✓
Adverse event		✓	✓	✓	✓	✓
Reasons of drop-outs or withdrawals		✓	✓	✓	✓	
Patient's compliance					✓	

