#### Recruitment

2.2.1

Patients will be recruited from the outpatient and inpatient gastrointestinal endoscopy departments of Shanghai Hospital of Integrated Traditional Chinese Medicine, Longhua Hospital affiliated with Shanghai University of TCM and Traditional Chinese Medicine Hospital of Shaanxi Province.

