#### Sample sizes

2.2.6

Based on the literature findigns, the control group treated with mesalazine showed a 12-week effective rate of 71 % [17], while the experimental group treated with JPQC recipe and mesalazine exhibited an effective rate of 94.12 % in 12 weeks [18]. Considering a clinical difference to improve the effective rate, with α set at a unilateral level of 0.05 and β at 0.10, the sample size calculation was performed using the formula$$n=\frac{{2\bar{p}\bar{q}\left(Z_{\alpha }+Z_{\beta }\right)}^{2}}{{\left(p1-p2\right)}^{2}}$$

This yielded a sample size of approximately 56 cases for each group (n1 = n2 ≈ 56 cases). Accounting for a dropout rate of 20 %, the study required a total of 140 cases, with 70 patients in the control group and 70 patients in the test group.

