### Statistical analysis

2.7

Statistical analysis will be conducted using SPSS 24.0 software. Descriptive statistics for measurement data will include mean ± standard deviation ($\bar{X}$ ± S) for data conforming to normal distribution. Two independent samples t-tests will be employed for comparing means, and variance analysis for multi-sample comparisons. Nonparametric tests will be used for data not conforming to normal distribution. Counting data will be analyzed using the χ^2^ test, and rank sum test for rank data. Correlation analysis between two variables will use linear correlation for bivariate normal distribution data and Spearman rank correlation for non-bivariate normal distribution or graded data. A significance level of *P* < 0.05 will be considered statistically significant. The study will also provide statistical descriptions of adverse events, adverse reactions, dropout rates, and rejections during treatment.

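### The between-arm tests named for this three-hospital trial carry no centre term; adding one gives a modest gain in precision at almost no cost

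*Protocol article*

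**What the plan says.** Section 2.1 describes the design: "This is a randomized controlled multicenter clinical trial comprising two parallel groups". Section 2.2.1 lists three recruiting hospitals: a Shanghai integrated-medicine hospital, then "Longhua Hospital affiliated with Shanghai University of TCM and Traditional Chinese Medicine Hospital of Shaanxi Province". No numbers per hospital are given.

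On allocation, section 2.1 says only that "eligible subjects will be randomly assigned to two groups in a 1:1 ratio". It does not say how the sequence is generated, or whether it is blocked or stratified.

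On analysis, section 2.7 states: "Two independent samples t-tests will be employed for comparing means, and variance analysis for multi-sample comparisons". For other data types it states: "Counting data will be analyzed using the χ^2^ test, and rank sum test for rank data". None of these statements mentions centre.

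**The concern.** Centre is known for every patient before treatment starts. Two of the hospitals are Shanghai institutions and the third is in another province, so outcome levels could plausibly differ between them. This applies to IBD-F, the graded TCM symptom scores and the stool microbiome and metabolite measures. The documents give no data on any such difference.

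If centres do differ, a two-sample test leaves that variation in its error term. What follows depends on how patients were allocated:

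- **Not stratified by centre.** The arm difference keeps the extra noise from chance differences in centre mix. The test is valid but less precise than it could be.
- **Stratified by centre.** The design has already removed that noise from the arm difference, but the t-test's standard error still includes it. The test is then conservative and gives up power that the design has earned.

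The stake is efficiency in both cases. Neither case produces excess false positives.

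**Working it through.** **Inputs from the documents.** Three centres (2.2.1); 1:1 allocation (2.1); unadjusted two-sample tests (2.7); 56 patients per arm before dropout and 70 per arm after it (2.2.6).

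**Inputs assumed.** The between-centre share of outcome variance, ρ, is taken from 0 to 0.20. Centre sizes in the simulation are 50%, 25% and 25%. Neither is in the documents.

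**Step 1: the plan's own figure.** Section 2.2.6 uses n = 2·p̄·q̄·(Zα + Zβ)² / (p1 − p2)², with rates 0.71 and 0.9412. So p̄ = 0.8256, q̄ = 0.1744 and the difference is 0.2312.

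- With the one-sided α stated there ("with α set at a unilateral level of 0.05 and β at 0.10"), n = 46.1, so 47 per arm. This does not reproduce 56.
- With a two-sided α of 0.05, n = 56.6, which is close to 56.
- The dropout step reproduces: 56 / 0.80 = 70 per arm, 140 in total.

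The α mismatch is a separate matter. This point takes from section 2.2.6 only 2 × 56 = 112 evaluable patients and a reference power of 90%. That power was planned for a response rate, not for IBD-F, so it is a yardstick here and not the trial's power for IBD-F.

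**Step 2: power gained by adjusting, analytically.** Adjusting for centre multiplies the residual variance by (1 − ρ). If the unadjusted two-sided 5% test has 90% power, the adjusted power is Φ[(1.960 + 1.282)/√(1 − ρ) − 1.960]. The number needed to keep 90% power is 112 × (1 − ρ).

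| ρ (assumed) | Adjusted power | Patients for 90% power |
|---|---|---|
| 0 | 90.0% | 112 |
| 0.02 | 90.6% | 110 |
| 0.05 | 91.4% | 106 |
| 0.10 | 92.7% | 101 |
| 0.20 | 95.2% | 90 |

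**Step 3: simulation, allocation not stratified.** 112 patients, 6,000 runs per setting, total variance 1. The arm difference is 0 or 0.613 SD, since (1.960 + 1.282) × √(4/112) = 0.613.

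- Mean error of the unadjusted arm difference: within 0.005 SD of zero at every ρ run (0, 0.05, 0.10, 0.20).
- Type I error of the unadjusted test: 4.6% to 5.2%.
- Power at ρ = 0: 89.5% unadjusted, 88.8% adjusted.
- Power at ρ = 0.05: 89.6% unadjusted, 90.8% adjusted.
- Power at ρ = 0.10: 90.0% unadjusted, 92.3% adjusted. The standard errors are about 0.188 and 0.181.
- Power at ρ = 0.20: 89.6% unadjusted, 94.5% adjusted. The standard errors are about 0.189 and 0.170.

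The adjusted figures fall slightly below those of Step 2 because the simulation includes the small cost of estimating centre effects. At ρ = 0 that cost is all that remains.

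**Step 4: simulation, allocation stratified by centre.** The variance of the arm difference is already reduced by (1 − ρ), but the t-test does not know it. Its type I error is therefore about 2Φ[−1.960/√(1 − ρ)].

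| ρ (assumed) | Formula | Simulated, unadjusted | Simulated, adjusted |
|---|---|---|---|
| 0.05 | 4.4% | 4.6% | 5.2% |
| 0.10 | 3.9% | 4.0% | 5.1% |
| 0.20 | 2.8% | 2.8% | 5.2% |

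The simulation error near 5% is √(0.05 × 0.95 / 6000) = 0.28 percentage points. The deficit at ρ = 0.05 is thus barely visible by simulation alone, while those at 0.10 and 0.20 are clear. Power at ρ = 0.10 was 89.9% unadjusted and 91.6% adjusted; at 0.20 it was 92.0% and 94.6%.

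**The case against.** The strongest reply is that an unadjusted t-test is valid in a randomised trial with three sites and 140 patients, so adjusting is only an efficiency preference. That stands, and it limits the point to a modest improvement.

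A second reply is that a condensed article leaves covariates and strata to the full protocol or analysis plan. This holds for stratification. It holds less well for the analysis, because section 2.7 does not merely omit a model: it names the tests. If an unseen plan contains a centre term, section 2.7 should be brought into line with it. The article's analysis of variance does not settle the matter, since it is tied to comparisons of several samples and the trial has two arms.

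A reader might also infer three stronger claims, none of which the documents support:

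- **That allocation ignores centre.** The article is silent; it does not say that the list is unstratified.
- **That site differences bias the arm contrast.** Randomisation prevents this, and Step 3 shows none. Chance imbalance within a site is sampling error that the standard error already covers. As an illustration, take an assumed 40-patient site split 24:16 with 70 per arm. The contrast shifts by 8/70 = 0.11 of that site's difference from the rest. For an assumed difference of 0.5 SD the shift is 0.06 SD, against a standard error of √(2/70) = 0.17 SD.
- **That each hospital dispenses its own JPQC product.** Section 2.3.1 says the herb pieces are "sourced from the hospital's herbal medicine room", in the singular and without naming the hospital. Supply from one hospital fits the words equally well. A centre main effect would not reveal a product difference in any case.

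**Conclusion.** The point holds as one of precision. Section 2.7 fixes unadjusted tests for a three-centre trial, and a centre-adjusted comparison is better at almost no cost.

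For centre shares of 2% to 10% the gain is about 1 to 3 percentage points of power, and at 20% about 5 points. At a share of 0 there is no gain and a trivial loss. If allocation turns out to be stratified by centre, adjustment also returns a conservative test to its nominal level.

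These sizes rest on the assumed variance shares, the assumed centre sizes, and the 90% reference power with 112 evaluable patients. A larger share for stool measures is conceivable, but nothing in the documents supports a figure. The stated analysis is neither biased nor prone to false positives.

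**What to change.** In section 2.7:

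- Replace the two-sample t-test for IBD-F and the other continuous outcomes, including stool measures, with a linear model containing arm and centre (three levels).
- Replace the plain chi-square test for between-arm comparisons of counts with a centre-stratified Mantel-Haenszel test.
- Where a rank-sum test is kept, use its centre-stratified form (van Elteren).

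The linear model is appropriate whether or not allocation is stratified by centre, so the change does not depend on the allocation scheme and alters nothing for patients already enrolled. The cost is a sentence or two in section 2.7 and two degrees of freedom. It should be made before the outcome data are examined by arm.
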